#### Standardized phone call and letters via post

Participants with COPD will also, irrespective of the originally assigned group (HIIT or MICT) and chosen setting, receive a phone call once every 14 days. Using a standardized call protocol (see additional file 4), we will gather the necessary information to progress training intensity and information about attendance and adherence to the exercise intervention. Every third month, information about symptoms of exacerbations will also be collected via phone call (see additional file 4). Participants with COPD will also be provided with a diary where they can document their training sessions and write down additional information, e.g., change in medication. Additionally, questions on health status (CAT) and disease-specific quality of life (chronic respiratory disease questionnaire (CRQ)) will be collected every third month by sending a letter with the questionnaires via the post that will be self-administered or by a phone call.

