#### Hospitalisations

Number of hospitalisations per participant. Time, cause, length of stay, and emergency room visits (with no hospitalization afterwards) and their cause will also be extracted. Hospitalizations and emergency room visits will be classified as respiratory or non-respiratory. Data on hospitalizations will be extracted from the participant’s medical record and, when available, cross-checked with the participant’s diary (an outcome measure only in phase 2).

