#### Exacerbations

Number of COPD exacerbations per participant (COPD only) during the trial period will be collected (an outcome measure only in phase 2).

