#### Mortality

Number of deaths will be extracted from the participant’s medical record. Time and cause of each death will also be extracted (an outcome measure only in phase 2).

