#### Muscle power and cardiorespiratory fitness

A sample size of 70 individuals (*n* = 35 per group) is also sufficient to detect a difference of 19.4% (SD 26.8%) [74] in quadriceps power (*n* = 30 per group) and to detect a relevant difference in maximal oxygen consumption (VO_2_max) of 3.5 mL/kg/min (SD 4.6 mL/kg/min) [119] (*n* = 26 per group) measured during a CPET. A difference of 3.5 mL/kg/min is associated with a 15% decrease in risk for cardiovascular disease [120]. No clinically relevant difference exists for muscle power; however, a difference of 19.4% is the minimal detectable change (MDC) from repeated testing of quadriceps peak power in older adults, as calculated by MDC = 1.96 × √2 × standard error of measurement (SEM) [74].

### Phase 2

In total, 138 individuals with COPD will be included in phase 2 (supramaximal HIT (*n* = 46), MICT (*n* = 46), and usual care (*n* = 46)). The sample size is estimated to account for an up to 30% additional drop-out rate at 24 months, in line with previous literature [121–123]. See phase 1 for complete details on the main sample size calculation. Additionally, as reported above in phase 1, the SD of 0.4 in the cognitive test battery is estimated from a trial in healthy adults comparing low to higher-intensity exercises [118] and not in patients with COPD. In phase 1, this uncertainty will be addressed with the increase in sample size from 70 to 92. However, for phase 2, we will instead perform an interim blinded sample re-estimation after half of the participants have performed baseline and 24-month follow-up, using recommended procedures for non-comparative data [124, 125], and adjust the sample size accordingly. These adaptations are recommended when there is any uncertainty in the SD. Importantly, using non-comparative data does not inflate the type I error probability or induce any bias in the treatment effect estimate (as it would if comparative data had been used) [124, 125].

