#### Statistical methods—outcomes

For primary and secondary outcomes with continuous data, treatment effect will be estimated by mean change-from-baseline (delta-value (Δ)) with 95% confidence intervals and the effect size (ES). The between-group effects will be analysed using analysis of covariance (ANCOVA). In the ANCOVA, baseline values, age, sex, centre, and VO_2_peak will be used as covariates. In phase 1, the primary analyses will be one model for the COPD group and one model for HC. In addition, to investigate any differential effects to the interventions between COPD and HC, a two-way ANCOVA including the Group (COPD/HC) × Intervention (supramaximal HIIT/MICT) interaction will be performed. In phase 2, there will be one model with the three arms (supramaximal HIIT, MICT, and usual care). Additional details will be provided in the SAP.

The assumptions of linearity, normality of residuals, and homogenous variance will be checked using residual plots, normal quantile plots, and histograms. Violations of linearity and normality assumptions will be dealt with by transformations of the dependent variable or non-linear modelling of the independent variables. Outliers will not be removed unless there is a methodological reason for it.

Feasibility of intervention outcomes and number of responders will be described with descriptive statistics and analysed with between group (HIIT/MICT) comparisons in both the COPD (phase 1 and 2) and HC group (phase 1).

In phase 1, hospitalization and exacerbations during the intervention will be presented descriptively. In phase 2, mortality, hospitalizations, and exacerbations will be presented with descriptive statistics and analysed using Kaplan–Meier curves and Cox proportional hazard models.

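### Phase 2 exacerbations and hospitalisations are defined as numbers per participant, but the only between-arm analysis named is Kaplan–Meier and Cox, which in standard form use first events only

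*Protocol article*

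**What the plan says.** The outcome definitions are in the protocol article under Hospitalisations and Exacerbations. The first reads "Number of hospitalisations per participant", followed by "Time, cause, length of stay, and emergency room visits (with no hospitalization afterwards) and their cause will also be extracted". The second reads "Number of COPD exacerbations per participant (COPD only) during the trial period will be collected". Both are marked as outcome measures for phase 2 only, and both are listed among the secondary objectives. Mortality is defined next: "Number of deaths will be extracted from the participant’s medical record".

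The analysis is fixed in one sentence under Statistical methods—outcomes: in phase 2 all three outcomes are to be summarised descriptively and "analysed using Kaplan–Meier curves and Cox proportional hazard models". Neither that section nor any other in the article names a Poisson, negative binomial or recurrent-event model, and none defines a time-to-first-event outcome. On numbers, the Phase 2 part of the sample size section says "In total, 138 individuals with COPD will be included in phase 2", which is 46 per arm, and allows for up to 30% additional dropout at 24 months.

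**The concern.** One sentence applies one method to three outcomes of two kinds. Death occurs at most once, so a time-to-event analysis suits it. Exacerbations and hospitalisations can recur, and their definitions ask how many each participant had. A standard Kaplan–Meier curve or Cox model asks how soon the first one came. A participant with one exacerbation and a participant with five contribute the same event information if their first events fall on the same day.

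Two things are at stake. First, the only inferential comparison of the arms would not address the outcome as defined, and a first-event hazard ratio could be read as the effect on the burden of events. Second, with 46 per arm before dropout, leaving repeat events unused can cost precision that the trial can hardly spare.

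**Working it through.** The article states no event rate, hazard ratio or power for these outcomes, so there is no figure of its own to reproduce. The mismatch itself follows from reading the definitions beside the analysis sentence. The arithmetic below only illustrates its size.

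**Inputs from the article:** 46 per arm; 24 months; two-sided alpha 0.05; up to 30% additional dropout.

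**Assumed inputs (not in the documents):** control rate r of 0.2, 0.5, 1.0 or 1.5 events per person-year; rate ratio 0.6; gamma variation between participants with dispersion k of 0.5 or 1.0.

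**Step 1: share of events a first-event analysis leaves unused, full follow-up.** The mean count is μ₀ = 2r in the control arm and μ₁ = 0.6 × 2r in the other. The share of participants with at least one event is P(μ) = 1 − (1 + kμ)^(−1/k). The unused share is 1 − [P(μ₀) + P(μ₁)] / (μ₀ + μ₁).

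| r per year | k | P(μ₀) | P(μ₁) | μ₀ + μ₁ | Unused |
|---|---|---|---|---|---|
| 0.2 | 0.5 | 0.306 | 0.203 | 0.64 | 21% |
| 0.2 | 1.0 | 0.286 | 0.194 | 0.64 | 25% |
| 0.5 | 0.5 | 0.556 | 0.408 | 1.6 | 40% |
| 0.5 | 1.0 | 0.500 | 0.375 | 1.6 | 45% |
| 1.0 | 0.5 | 0.750 | 0.609 | 3.2 | 58% |
| 1.0 | 1.0 | 0.667 | 0.545 | 3.2 | 62% |
| 1.5 | 0.5 | 0.840 | 0.723 | 4.8 | 67% |
| 1.5 | 1.0 | 0.750 | 0.643 | 4.8 | 71% |

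In numbers of events: at 1 per year a control arm of 46 has 46 × 2 = 92 expected events. Of these, 46 × 0.750 = 34.5 (k = 0.5) or 46 × 0.667 = 30.7 (k = 1.0) are first events. In simulated trials, with and without 30% dropout, the unused share is about 36–71% at 0.5–1.5 per year and about 18–24% at 0.2 per year. Shorter follow-up lowers it slightly.

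**Step 2: power.** Simulated two-arm comparisons, 400 trials per scenario, full follow-up, first-event Cox against negative binomial on the same data:

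| r per year | k | Cox | Negative binomial |
|---|---|---|---|
| 0.5 | 0.5 | 31% | 44% |
| 0.5 | 1.0 | 25% | 39% |
| 1.0 | 0.5 | 40% | 67% |
| 1.0 | 1.0 | 24% | 50% |
| 1.5 | 0.5 | 37% | 74% |
| 1.5 | 1.0 | 26% | 58% |

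With 30% dropout the ranges were 19–41% and 34–69%. Monte Carlo error is up to √(0.5 × 0.5 / 400) = 2.5 points, so the ends of the ranges are good to a few points only. One run at 0.5 per year, k = 1.0 and 30% dropout gave 21% and 31%. At 0.2 per year power was about 15% against 17–19%: both analyses are uninformative and the difference is near simulation error.

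**Step 3: what the two analyses estimate.** With a true rate ratio of 0.60, the average first-event hazard ratio was 0.63–0.72. With a true ratio of 0.70 it was about 0.70 without variation between participants and 0.74–0.80 with k of 0.5–1.0. The hazard ratio is therefore not, in general, the ratio of the counts.

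**The case against.** **The article never says first event.** Recurrent-event extensions belong to the Cox family, and a separate SAP is promised. This is fair as far as it goes: the restriction to first events comes from the standard meaning of the named methods. But no extension is named, the Kaplan–Meier curves in the same sentence are naturally read as first-event curves, and the article has already chosen a method. It is a stated choice that does not match the stated outcome, not a detail left open.

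**Counts are not lost.** The same sentence promises descriptive statistics. This stands: what is missing is inference between arms on the counts.

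**The size is chosen, not derived.** This also stands. The eligibility criteria admit participants without marked symptoms if they are inactive, and exclude a recent exacerbation, so low rates are plausible, above all for hospitalisation. There the practical loss is small. The simulated data also follow the negative binomial model, which favours that analysis.

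Three stronger readings are tempting, and the documents do not support them:

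- *That exacerbation dates will not be available.* A reader might infer this because time is listed for hospitalisations and deaths but not for exacerbations, and because "Every third month, information about symptoms of exacerbations will also be collected via phone call". The call form is in a supplement not shown here, participants keep a diary, and the per-protocol definition requires at least late exacerbations to be dated.
- *That death is mishandled as censoring.* Negative binomial regression with a follow-up offset also ends exposure at death, so the point does not favour the change. Censoring at death is also legitimate for a cause-specific Cox hazard.
- *That Cox biases the effect towards the null.* The gap in step 3 partly reflects a different estimand, not simply an error of estimation.

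**Conclusion.** The point holds in a limited form. For two phase 2 outcomes defined as numbers per participant, the only named between-arm analysis is one that, as normally applied, uses first events. That does not estimate the stated outcome and leaves repeat events out of the inference. This conclusion needs no assumption about rates.

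The size does. At assumed control rates of 0.5–1.5 per year, dispersion 0.5–1.0 and a rate ratio of 0.6, roughly 36–71% of events are unused and the power gap is material. At about 0.2 per year it is negligible. Even the better analysis stays below 80% power in every scenario examined. Both outcomes are secondary and unpowered, and the usual care arm is not randomised, so no primary conclusion depends on this. It should be corrected, but it is not critical.

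**What to change.** Split the sentence under Statistical methods—outcomes. For the numbers of exacerbations and hospitalisations, specify negative binomial regression with log follow-up time as offset, trial arm and the planned covariates, reporting rate ratios with 95% confidence intervals. Keep Kaplan–Meier and Cox for mortality, and for the other two outcomes as a supportive analysis labelled time to first event.

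The cost is a change of wording in the protocol or the SAP, which the article says will be finalised before database lock. No new data or participants are needed. The downside is small: one more model per outcome and an assumed count distribution. If events prove rare the dispersion may be poorly estimated, so it is worth naming a fallback in advance, such as Poisson regression with robust standard errors.

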### Participants and recruitment

We will recruit participants with COPD via primary and specialist health care or advertisement. Matched healthy controls will be recruited via advertisement. All advertisements will have approval by the regional ethical board and will be disseminated via billboards, newspapers, local organization contacts, or targeted social media (e.g., Facebook). Each participant will receive financial compensation in an amount determined by the local centre and ethical board. If a participant would drop out, payments will be pro-rated based on the length of time stayed or the number of visits performed in the trial.

The planned distribution of participants per centre is as follows: in Umeå, approximately two-thirds (*n* = 138) of the participants will be recruited and in Hasselt the remaining third (*n* = 70) of participants. Subsequently, 92 individuals with COPD (HIIT: *n* = 31, MICT: *n* = 31, usual care: *n* = 30) and 46 HC (HIIT: *n* = 23, MICT: *n* = 23) are planned to be recruited in Umeå, while 46 individuals with COPD (HIIT: *n* = 15, MICT: *n* = 15, usual care: *n* = 16) and 24 HC (HIIT: *n* = 12, MICT: *n* = 12) are planned to be recruited in Hasselt. The enrolment period is expected to extend over approximately 24 months.

Written informed consent will be obtained by the assessors (AN, JJ, JDB, and DC) trained in Good Clinical Practice after all procedures have been explained, before the start of the trial during participants’ first test day.

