### Eligibility criteria

The inclusion criteria are as follows:60 years of age or olderIndependent in activities of daily livingFor people with COPD: post-bronchodilator spirometry confirmed COPD diagnosis (forced expiratory volume in one second (FEV_1_) to forced vital capacity (FVC) ratio < 0.70) [2].For people with COPD: symptomatic (COPD assessment test (CAT) ≥ 10 or modified Medical Research Council dyspnoea scale (mMRC) ≥ 2) or not being regularly physically active at a moderate or high intensity over the last year defined as not meeting WHO requirements for physical activity [46].For healthy controls: normal lung function

The exclusion criteria are as follows:

Movement-related, cardiovascular, neuromuscular, metabolic, skeletal and/or rheumatic conditions, and diseases that are unstable and/or prohibit exercise or tests, based on screening by a physician. For example, but not limited to:
Musculoskeletal pain prohibiting participation in physical tests and exerciseRecent myocardial infarction, coronary artery bypass grafting, angioplasty, or other cardiac eventsUncontrolled arterial hypertensionPathological ECG-findings during CPETOther lung conditions, including but not limited to uncontrolled or very severe asthma, interstitial lung disease, lung cancer, pulmonary hypertension, pulmonary vascular disease, and pulmonary fibrosis.

Medical conditions and treatments with known effects on brain function and cognition, for example:f)Previous trauma to the head with lasting cognitive or symptom-related issuesg)Physical or mental disabilitiesh)Neurological condition (dementia, multiple sclerosis, stroke)i)Psychiatric illness not including depression or general anxiety disorderj)Severe cognitive impairmentk)Recent or current cancer diagnosis and treatmentl)For those accepting MRI or PET/CT: metal implants, pacemakers, claustrophobia, and other MRI-incompatible factors.m)Inability to read or speak Swedish (Umeå participants), Dutch, French (Hasselt participants), or English (Umeå and Hasselt participants)

For people with COPD:n)Comorbid conditions that limit exercise performance to a greater extent than the COPD diagnosis.o)Currently participating in a pulmonary rehabilitation program or have been involved in pulmonary rehabilitation in the last 12 months.p)Experienced a COPD exacerbation that led to a change in medication dosage or frequency in the preceding 6 weeks.

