**Visit 5**																			
PET/CT^e^							X												X
I**nterventional**																			
Feasibility^c^									X						X				
Adverse events									X						X				
Exacerbations / hospitalisations / mortality									X						X				

Schedule of enrolment, interventions and assessments. The number of weeks can vary slightly depending on schedueling and thus time needed for follow-up assessments (2-3 weeks) and weeks of rest before starting the phase 2 (1-2 weeks). The schedule is representative for participants in Umeå, Sweden, minor differences exist for participants in Hasselt, Belgium, due to logistics

*HIIT* supramaximal high-intensity interval training, *MICT* moderate intensity continuous training, *mMRC* Medical Research Council Dyspnea Scale, *MoCA* the Montreal Cognitive Assessment test, *CPET* cardiopulmonary exercise test, *BCST* Borg cycle strength test, *CAT *COPD assessment test, *CRQ* Chronic Respiratory Disease Questionnaire, *HADS* Hospital Anxiety and Depression Scale, *MNA* Mini-Nutritional Assessment, *PET/CT* positron emission tomography/computed tomography

^a^only mMRC is used for screening

^b^only CAT is used for screening

^c^not for usual care group

^d^not for HC group

^e^only for those enrolled at Umeå, Sweden

^f^(superscripted) MoCA is only performed at baseline at 24-months

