*Markers of systemic inflammation.* Markers of systemic inflammation, including but not limited to highly sensitive C-reactive protein (hs-CRP [mg/L]), fibrinogen (g/L), interleukin-6 (IL-6), IL-8, and tumour necrosis factor alpha (TNF-α), are measured in pq/L.*Markers of cardiometabolic health and blood lipid profile.* Total cholesterol, low-density lipoprotein (LDL), high-density lipoprotein (HDL), non-HDL, triglycerides, and glucose measured in mmol/L, insulin (mIU/L), and haemoglobin A1c (HbA1c, [%]). Glucose and insulin levels will be used to calculate the Homeostatic Model Assessment for Insulin Resistance (HOMA-IR) [90].*Complete blood count with differential.* A differential blood count will be performed to primarily analyse the total white blood cell count and eosinophil count in whole blood (count × 10^9^/L), which is related to inflammation and exacerbations in people with COPD [91].*Epigenetic modifications and genotyping.* Genome-wide DNA methylation (differentially methylated cytosines) will be analysed via the EPICarray technology following manufacturer’s guidelines at H42, a company specialized in epigenetic analysis, based at the Faculty of Pharmaceutical Sciences of Ghent University (Belgium). We will also do a targeted genotyping approach for *APOE*, known to be related to cognitive function [92].*Blood sample procedures*. Fasted venous blood samples will be collected in a seated position with a 21–22-gauge needle from the antecubital fossa or back of the hand. Blood samples will be collected between 7.45 and 10.30 AM after a 15-min seated rest. Per every time point, the blood is collected into three K_2_EDTA tubes, one serum-separator tube (SST), one lithium–heparin tubes, and one citrate tube (BD Vacutainer, Franklin Lakes, NJ, USA). A total of approximately 30 mL of blood will be collected per time point. Tubes will be immediately homogenized by inverting five to ten times, as appropriate depending on type of tube. One EDTA tube, and the citrate plasma tube, will be immediately sent for analysis (complete blood count and fibrinogen, respectively) and not undergo cryopreservation. The remaining tubes will be sent to the local biobank, and after 30 min at room temperature to allow for clotting in the SST, the tubes will be centrifuged at 1500 × *g* for 10 min (whole blood samples will be aliquoted from EDTA tube before centrifugation). Samples will then be aliquoted into serum, plasma (EDTA and lithium-heparin), erythrocytes (EDTA), and buffy coat (EDTA). Aliquots of 200–500 µL will be stored in − 80°C within 1 h of blood collection.

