In phase 2, pre-specified longitudinal mediation analyses will be performed on the entire MRI and PET/CT sample between changes in VO_2_peak, neurodegenerative measures, such as cognitive function and hippocampal volume and inflammation levels between baseline and 24 months. In these models, we will determine how inflammation mediates the effect of exercise training on neurodegenerative measures, including global cognitive function, hippocampal volume, and grey matter in the posterior, anterior, and midcingulate cingulate cortex, respectively, using a set of linear regression and maximum likelihood estimations [132]. Additionally, we will test whether the exercise training intensity (supramaximal HIT vs. MICT) has a different mediating effect. Additional details will be provided in the SAP.

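### The phase 2 mediation models on global cognition are tied to the MRI and PET/CT sample, although those with a blood inflammation mediator need no scan

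*Protocol article*

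**What the plan says.** In the protocol article, the section on statistical methods for outcomes announces that the phase 2 "pre-specified longitudinal mediation analyses will be performed on the entire MRI and PET/CT sample". The same paragraph says that in these models "we will determine how inflammation mediates the effect of exercise training on neurodegenerative measures, including global cognitive function", followed by hippocampal volume and cingulate grey matter. No separate sample is named for the cognition models. The paragraph ends with "Additional details will be provided in the SAP".

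Other sections determine who is in that sample and who has the data:

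- **Phase 2 size.** "In total, 138 individuals with COPD will be included in phase 2", with 46 in each of the three arms (Sample size, Phase 2).
- **PET/CT.** Footnote e of Table 5 marks it as "only for those enrolled at Umeå, Sweden".
- **MRI.** A scanner is named for each centre, and the MRI row of Table 5 carries no centre footnote.
- **Scanning is optional.** One exclusion criterion begins "For those accepting MRI or PET/CT: metal implants, pacemakers", so a person can be in the trial without being scanned. No acceptance rate is given.
- **Blood.** "Markers of systemic inflammation, including but not limited to highly sensitive C-reactive protein" are measured, together with fibrinogen, IL-6, IL-8 and TNF-α. The blood sampling row of Table 5 has no centre or arm footnote. Neither has the row for global cognition or the row for the cardiopulmonary exercise test.

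**The concern.** The paragraph sets one sample for a family of models that need different data. A model from exercise through circulating inflammation to global cognition uses the allocated arm, the blood markers and the cognitive battery, plus VO2peak if it is included. None of these comes from a scanner. Requiring a scan for that model has two costs:

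- **Precision.** People with both mediator and outcome measured are left out.
- **Selection.** Those who remain accepted imaging and had no pacemaker, metal implant, claustrophobia or similar obstacle. The article gives nothing from which the direction of any resulting bias could be worked out.

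The wording also leaves two things open. The sample could mean both scans or either scan, and the mediator could be blood-based or PET-based. An analysis called pre-specified could thus be run in one centre with at most 92 people or in two centres with up to 138.

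The role of inflammation in neurodegeneration is part of the stated aim of phase 2 (Abstract; Background and rationale), so these models matter even though they are mechanistic.

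**Working it through.** **Inputs.** Umeå plans "92 individuals with COPD (HIIT: *n* = 31, MICT: *n* = 31, usual care: *n* = 30"; Hasselt plans 15, 15 and 16 (Participants and recruitment). The article states no size for the MRI, PET/CT or mediation sample.

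**Step 1: reproduce the stated counts.** 31 + 31 + 30 = 92; 15 + 15 + 16 = 46; 92 + 46 = 138. This agrees with the phase 2 total.

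**Step 2: which models need a scan.**

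| Mediator | Outcome | Scan needed | Largest possible sample |
|---|---|---|---|
| Blood inflammation | Global cognition | none | 138, both centres |
| Blood inflammation | Hippocampal volume, grey matter | MRI | all with MRI, both centres |
| PET uptake | Global cognition | PET/CT | 92, Umeå |
| PET uptake | Hippocampal volume, grey matter | both | 92, Umeå |

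Only the first row loses data that could have been used.

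**Step 3: loss for the first row under each reading.** Let a be the share accepting the scan. Only a = 100% involves no assumption about refusal; the other rates are assumptions. Loss = 1 − n/138. The standard error ratio is √(138/n), assuming the same residual variance and arm split in the subset.

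| a | PET/CT required: n = 92a | Loss | SE ratio | MRI enough: n = 138a | Loss | SE ratio |
|---|---|---|---|---|---|---|
| 100% | 92 | 33% | 1.22 | 138 | 0% | 1.00 |
| 90% | 82.8 | 40% | 1.29 | 124.2 | 10% | 1.05 |
| 75% | 69 | 50% | 1.41 | 103.5 | 25% | 1.15 |

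Under the first reading one third is the minimum loss. Under the second the loss can be zero.

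**Step 4: the HIIT versus MICT comparison of mediation.** With PET/CT required, 31 + 31 = 62 of the 92 exercising participants remain. The loss is 30/92 = 33% and the SE ratio is √(92/62) = 1.22, so the relative loss is the same.

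**Step 5: detectable association.** The smallest correlation detectable with 80% power at two-sided 0.05 is r = tanh[(1.960 + 0.842)/√(n − 3)].

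- No drop-out: n = 138 gives 0.237; n = 92 gives 0.289.
- With 30% drop-out: n = 0.7 × 138 = 96.6 gives 0.282; n = 0.7 × 92 = 64.4 gives 0.343.
- If the approximately 15% at 3 months is also applied: n = 0.595 × 138 = 82.1 gives 0.305; n = 0.595 × 92 = 54.7 gives 0.371.

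These figures are for a single path, as a yardstick. They are not the power of an indirect effect, which would need path sizes that the article does not give.

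**The case against.** The strongest objection is that the article leaves further detail to the SAP, and which participants enter which mediation model is commonly settled there. This stands for the details. It does not dispose of the point, because the article states a sample and then lists global cognition among the outcomes analysed in it. An SAP that follows the article carries the restriction over.

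Second, the sample may be meant inclusively, as everyone with the relevant scan. MRI is done at both centres, so Hasselt would then be included. This stands. A reader might infer that a third or more of the usable sample is discarded outright. The documents do not support that: the figure holds only if PET/CT is required, and the article does not say so.

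Third, the article says only inflammation. If PET uptake is the mediator, the restriction to PET/CT participants is unavoidable; for hippocampal volume and grey matter an MRI is needed whatever the mediator. This also stands, and it narrows the point to one combination of mediator and outcome.

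Fourth, a common sample lets the cognition and brain-structure pathways be compared in the same people. That is a fair reason to report such an analysis, and a sensitivity analysis meets it. It is no reason to have only that version.

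Last, a reader might infer that the test of a primary outcome is weakened. It is not: cognition at 24 months is analysed by the three-arm ANCOVA, under intention to treat when applicable and with multiple imputation. The mediation paragraph does not restrict that analysis.

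**Conclusion.** The point holds for mediation models with a blood inflammation mediator and global cognition as outcome. As worded, the plan runs them in people with imaging although no image is needed, and it leaves both the imaging sample and the mediator undefined.

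The size depends on the reading. If PET/CT is required, at least 46 of 138 (33%) are lost and standard errors are about 22% larger. Otherwise the loss is the share without MRI: none at full acceptance, 10% at 90% and 25% at 75%, all assumed rates. The standard error figures also assume similar variance in the scanned and unscanned. Selection of people willing and able to be scanned arises under either reading whenever some are not scanned; its direction cannot be derived from the article.

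The change is worth making because it gains precision and reduces selection whenever some participants are not scanned. It concerns mechanistic analyses and does not touch the primary comparison.

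**What to change.** State in the SAP, and in any protocol amendment, which inflammation measure is the mediator in each model, and define the sample per model:

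1. Blood inflammation to global cognition: all phase 2 COPD participants at both centres, with missing values handled by the multiple imputation already planned.
2. Blood inflammation to hippocampal volume or grey matter: all participants with MRI, at both centres.
3. Any model using 11C-deprenyl uptake: the Umeå PET/CT sample, and with MRI as well where the outcome is structural.
4. Sensitivity analysis: the cognition model of item 1 repeated in the imaging sample, so that pathways can be compared in the same people. Say whether this sample means MRI, PET/CT or both.

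Report the number scanned by centre and arm alongside these models.

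The cost is wording, with no new data, visits or participants. The article plans to finalise the SAP before database lock and unblinding, which leaves room for the change.
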